#### Secondary outcomes

2.5.2

① Recovery of the K-HDRS (The percentage of participants whose K-HDRS improved >50%): Recovery in the last observed K-HDRS during the 8 weeks of treatment.

② Remission of K-HDRS (The percentage of participants whose K-HDRS improved to a score <7): remission in the last observed K-HDRS during the 8 weeks of treatment.

③ K-BDI-II: Changes in K-BDI-II comparing the baseline and the last observed score during the 8 weeks of treatment.

④ KSCL-95: Changes in KSCL-95 comparing the baseline and the last observed score during the 8 weeks of treatment.

⑤ ISI: Changes in ISI comparing the baseline and the last observed score during the 8 weeks of treatment.

⑥ STAI-K: Changes in STAI-K comparing the baseline and the last observed score during the 8 weeks of treatment.

⑦ STAXI-K: Changes in STAXI-K comparing the baseline and the last observed score during the 8 weeks of treatment.

⑧ Instrument on Pattern Identifications for Depression: Changes in Instrument on Pattern Identifications for Depression score, comparing the baseline and the last observed score during the 8 weeks treatment.

⑨ EuroQol-5 dimension (EQ-5D): Changes in the EQ-5D comparing the baseline and the last observed score during the 8 weeks of treatment.

10. Melatonin & Cortisol Study: Changes in the concentration of melatonin and cortisol comparing the baseline and the last observed score during the 8 weeks of treatment.

#### Safety evaluation

2.5.3

Every participant given the medication at least once will be assessed for occurrence of adverse events and their association with the medication. Potential adverse events include all medical symptoms that will occur during the trial. Every unintended phenomenon, side effects, abnormalities in vital signs, and lab tests will be documented in an adverse events report. The investigator responsible will assess the adverse events at different stages based on their seriousness. The adverse events will be documented to be communicated to the participants and/or their legal representatives immediately and will be notified to the IRBs.

### Analysis of adherence

2.6

Use of the medications will be recorded at each visit for assessing drug compliance and documented in the case report form. Drug compliance will be estimated as follows. 

### Statistical methods

2.7

#### Sample size

2.7.1

The sample size required is based on results of the t-test for independent samples comparing changes in the K-HRDS score from baseline to the last observed one during the 8 weeks of treatment between the SOCG medium dose group and the placebo group.

Because no relevant results of clinical trials have been reported, the sample size was calculated referring to a clinical trial of similar design involving patients with depression.^[15]^

The sample size of each group is 37, considering a significance level of 5%, a power of 80%, and assigning a ratio of 1:1:1:1 and a dropout rate of 5%.

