#### Statistical analysis

2.7.2

The efficacy will be evaluated based on intention-to-treat (ITT) analysis and per-protocol (PP) analysis. Participants with total drug compliance <75% will be excluded from PP analysis.

Continuous data will be represented by mean, standard deviation, minimum, and maximum and categorical data will be represented by a frequency table. We will compare data using analysis of variance (ANOVA) for the continuous variables, and Pearson chi-squared test or Fisher's exact test for the categorical variables. The size of the type I error caused due to multiple comparisons will be modified using Bonferroni's method.

The primary outcome, the changes in the K-HRDS, will be evaluated using analysis of covariance (ANCOVA) with the experimental group, baseline K-HDRS, and the institution as the explanatory variables. The estimates of mean differences between placebo and each SOCG group, the 95% confidence interval, and the *P*-value will be presented. For evaluating the sensitivity of missing values of K-HDRS, the primary outcome observed at each point will be analyzed using the linear mixed model. The explanatory variables include all groups, baseline K-HDRS, institutions, the observation time point, and the interaction term of the experimental group based on the observation time point.

Among the secondary outcomes, recovery rate and remission rate of K-HDRS will be analyzed using logistic regression analysis with the experimental group, baseline K-HDRS, and the institution as the explanatory variables. Estimates of odds ratio of each SOCG group, 95% confidence interval, and *P*-value will be presented using the placebo group as the standard category. The other secondary outcomes will be analyzed using ANCOVA with the experimental group, baseline outcomes, and the institution as the explanatory variables.

For safety assessment, outcomes of lab tests will be compared to the baseline values. Each adverse event will be listed with a detailed explanation, and the frequency will be recorded separately based on correlation with the medication. Adverse events will be summarized based on groups and organs. The ANOVA or Kruskal-Wallis test will be used to compare the frequency of medication-correlated adverse events between groups. The Pearson chi-squared test or Fisher's exact test will be used to compare the percentage of participants who experienced the adverse events at least once between the groups.

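### The stated 80% power rests on one t-test at an unadjusted 5%, yet the plan invokes Bonferroni and tests three doses against placebo without saying at what level

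*Protocol article*

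**What the plan says.** **Sizing (Protocol article, section 2.7.1, Sample size).** The calculation is "based on results of the t-test for independent samples comparing changes in the K-HRDS score" "between the SOCG medium dose group and the placebo group". The result is given as "The sample size of each group is 37, considering a significance level of 5%, a power of 80" per cent, "assigning a ratio of 1:1:1:1 and a dropout rate of 5" per cent. No multiplicity divisor appears and sidedness is not stated. The assumed difference and SD are not printed; "the sample size was calculated referring to a clinical trial of similar design involving patients with depression".

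**Analysis (section 2.7.2, Statistical analysis).** The paragraph on descriptive statistics, ANOVA and chi-squared or Fisher tests ends with: "The size of the type I error caused due to multiple comparisons will be modified using Bonferroni's method". The next paragraph sets the primary analysis as an ANCOVA with group, baseline score and institution. Its output is "The estimates of mean differences between placebo and each SOCG group, the 95% confidence interval" and the P-value. With three active arms (section 2.1) that makes three primary contrasts.

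Neither section names medium dose against placebo as the only confirmatory test, and neither sets a testing order.

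**The concern.** The power statement and the multiplicity statement do not fit together. Power is claimed for one test at the full 5%. The analysis has three tests of the same outcome against a shared placebo arm, together with an unrestricted sentence that such multiplicity is handled by Bonferroni. If that sentence reaches the primary contrasts, the test of medium dose against placebo is not run at the level used to size it. If it does not, nothing in the text controls the type I error across the three primary tests.

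The first reading raises the chance of missing the planned effect in the sized comparison from the stated 20% to about 35%. The second raises the chance of at least one false positive dose from 5% to about 12.5%. The Abstract and Discussion intend the result to support a phase III trial and a choice of dose, so readers need to know which applies.

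**Working it through.** **Inputs from section 2.7.1:** 37 per group, 5% dropout, alpha 5%, power 80%, two-sample t-test. **From sections 2.1 and 2.7.2:** three dose-placebo contrasts; Bonferroni, divisor not given. **Assumed:** the 5% is two-sided (one-sided is also tried).

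**1. The plan's own figure.** The difference and SD are not printed, so 37 cannot be derived from scratch. The dropout step is consistent: 35 / 0.95 = 36.8, rounded up to 37, so 35 evaluable per group.

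**2. Implied effect.** Take the stated 80% at 5% as true and solve the noncentral t for the standardised difference d, with n = 35 per group and df = 2 × 35 − 2 = 68. This gives d = 0.679, with noncentrality d × √(n/2) = 0.679 × √17.5 = 2.84.

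**3. Same n and d at 0.05/3 = 0.0167.** The critical value rises from 1.995 to 2.455, and power falls to **65.1%**. With the SD pooled over four arms (136 df) it is 66.2%. Normal approximation as a check: Φ(1.960 + 0.842 − 2.394) = Φ(0.408) = 65.8%.

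**4. Sensitivity.**

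| Variation | Power, medium dose v placebo |
|---|---|
| Divisor 2 | 70.8% |
| Divisor 3 | 65.1% |
| Divisor 6 (all pairs) | 55.2% |
| Divisor 3, evaluable n of 34 to 37, d re-solved each time | 65.1% to 65.8% (t and z) |
| Divisor 3, d from n = 35, all 37 analysed | 68.1% |
| Divisor 3, 5% taken as one-sided (d = 0.600) | 63.4% |

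The result hardly depends on the unprinted effect size, because d is solved from the stated power. The loss comes from the change in alpha alone.

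**5. Size needed for 80% at 0.0167.** 47 evaluable per group; 47 / 0.95 = 49.5, so 50 randomised per group (200 in total, against 148).

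**6. What ANCOVA could recover.** Adjusting for baseline multiplies the residual variance of the change score by (1 − ρ²), where ρ is the correlation between baseline and change. The effective difference becomes 0.679 / √(1 − ρ²). The document gives no ρ, so these are assumed values, at 0.0167 with n = 35:

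| Assumed ρ | Power |
|---|---|
| 0 | 65% |
| 0.3 | 70% |
| 0.4 | 74% |
| 0.5 | 79% |
| 0.52 | 81% |

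A correlation slightly above 0.5 would restore the full 80%.

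**7. If the primary contrasts are not adjusted.** Three two-sided 5% tests sharing one placebo arm (pairwise correlation 0.5), simulated under no effect: at least one rejection in **12.5%** of trials.

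**8. At least one dose significant.** With divisor 3, if all three doses have the assumed effect: about 87% (simulated, normal approximation).

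**The case against.** **Bonferroni may not reach the primary analysis.** The sentence closes the paragraph on ANOVA and chi-squared tests and may mean pairwise follow-up of those. The ANCOVA paragraph does not repeat it, and its 95% intervals match an unadjusted 5% test. This stands as a limit: 0.05/3 for the primary contrasts is the natural reading of an unrestricted sentence, but it is not written. It does not remove the problem, because the alternative leaves the primary outcome with a family-wise error of about 12.5%.

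**The divisor and testing order may be in the full protocol or SAP.** They may, and their absence from an article would not by itself be a point. The point is that the two statements the article does make give no common level for the sized test.

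**A reader might infer that the design simply lacks its stated power and has 65%.** The document does not support that. The 80% is claimed for a change-score t-test at 5%, and nothing shows it to be wrong for that test. The planned test is an ANCOVA, which may recover some or all of the loss. An unseen calculation already run at 0.05/3 would show no shortfall (d of about 0.79), but section 2.7.1 says "considering a significance level of 5" per cent.

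**A reader might also infer that the phase III decision carries a one-in-three risk of a miss.** That goes too far. About 65% is the power for one given contrast. The chance that at least one dose succeeds is about 87% if all three have the assumed effect. That is not the quantity section 2.7.1 claims, however, and it does not repair the claim for the medium dose.

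**Conclusion.** The concern holds in conditional form. The article states 80% power at an unadjusted 5% for one contrast, then plans three contrasts with a Bonferroni statement whose reach and divisor are not given.

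- **If Bonferroni covers the three primary contrasts:** about 65% per comparison on the t-test basis (71% with divisor 2, 55% with divisor 6), instead of 80%. This assumes a two-sided 5%, 35 evaluable per group, and that the stated 80% is right at 5%. The ANCOVA gain is unknown.
- **If it does not:** a family-wise error of about 12.5% on the primary outcome.

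The text needs correcting under either reading. This should be fixed, but it is not fatal: no printed calculation is shown to be wrong, the trial is a phase II dose-finding study, and no additional participants are required.

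**What to change.** Keep 37 per group and choose one of two wordings in sections 2.7.1 and 2.7.2, carried through to the SAP.

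**(a) Keep Bonferroni.** State that 0.05/3 applies to the three primary dose-placebo contrasts. Restate the power for medium dose against placebo as 80% unadjusted and about 65% adjusted, both on the t-test basis. Give confidence intervals that match the adjusted level (1 − 0.05/3 = 98.3%). Cost: a less favourable power figure.

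**(b) Use a fixed sequence for the primary outcome.** Before unblinding, specify medium dose against placebo first at two-sided 5%, then the other two doses in a set order, each tested only if the preceding test is significant. This keeps the stated 80% for the sized comparison and controls family-wise error at 5%. Cost: no formal claim for the other doses if the first test fails.

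Under either option, state whether the 5% is one- or two-sided. The change is about one paragraph of text.

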#### Statistical analysis

2.7.2

The efficacy will be evaluated based on intention-to-treat (ITT) analysis and per-protocol (PP) analysis. Participants with total drug compliance <75% will be excluded from PP analysis.

Continuous data will be represented by mean, standard deviation, minimum, and maximum and categorical data will be represented by a frequency table. We will compare data using analysis of variance (ANOVA) for the continuous variables, and Pearson chi-squared test or Fisher's exact test for the categorical variables. The size of the type I error caused due to multiple comparisons will be modified using Bonferroni's method.

The primary outcome, the changes in the K-HRDS, will be evaluated using analysis of covariance (ANCOVA) with the experimental group, baseline K-HDRS, and the institution as the explanatory variables. The estimates of mean differences between placebo and each SOCG group, the 95% confidence interval, and the *P*-value will be presented. For evaluating the sensitivity of missing values of K-HDRS, the primary outcome observed at each point will be analyzed using the linear mixed model. The explanatory variables include all groups, baseline K-HDRS, institutions, the observation time point, and the interaction term of the experimental group based on the observation time point.

Among the secondary outcomes, recovery rate and remission rate of K-HDRS will be analyzed using logistic regression analysis with the experimental group, baseline K-HDRS, and the institution as the explanatory variables. Estimates of odds ratio of each SOCG group, 95% confidence interval, and *P*-value will be presented using the placebo group as the standard category. The other secondary outcomes will be analyzed using ANCOVA with the experimental group, baseline outcomes, and the institution as the explanatory variables.

For safety assessment, outcomes of lab tests will be compared to the baseline values. Each adverse event will be listed with a detailed explanation, and the frequency will be recorded separately based on correlation with the medication. Adverse events will be summarized based on groups and organs. The ANOVA or Kruskal-Wallis test will be used to compare the frequency of medication-correlated adverse events between groups. The Pearson chi-squared test or Fisher's exact test will be used to compare the percentage of participants who experienced the adverse events at least once between the groups.

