### Study design and setting

2.1

The study is designed as a Phase II clinical trial and is following a randomized, double blinded, placebo controlled, parallel design to examine the efficacy of SOCG in MDD treatment.

Participants will be selected from volunteers based on demographic information, medical history, vital signs, lab examinations, and selection criteria. Selected participants will be assigned to 3 experimental groups and 1 placebo group according to the stratified block randomization. The experimental groups will be a low dose group, a medium dose group, and a high dose group. Participants will be given SOCG or placebo 3 times/day, for 8weeks (56 days). They will be examined using the Korean Version of the Hamilton Depression Rating Scale (K-HDRS), the Korean version of the Beck Depression Inventory-II (K-BDI-II), Korean Symptom Check List-95 (KSCL-95), State Trait Anxiety Inventory-Korean version (STAI-K), State Trait Anger Expression Inventory Korean version (STAXI-K), Insomnia Severity Index (ISI), Instrument on Pattern Identifications for Depression, EuroQol-5 Dimension (EQ-5D), and melatonin and cortisol levels to assess score variation, improvements in quality of life, and biological indicators.

The research progress is summarized in Figure 1 and the examination details followed by visit schedules are shown in Table 1. Each visit should occur at the scheduled date or within ±4 days. The screening tests will be completed 10 days before the second visit (0 week). The results will be examined at the second visit. The lab tests will include hematologic tests for levels of hemoglobin, hematocrit, red blood cell count, white blood cell count, platelet count, and erythrocyte sedimentation rate, and hematochemical tests for levels of aspartate aminotransferase (AST), alanine aminotransferase (ALT), gamma-glutamic transpeptidase (γ-GTP), alkaline phosphatase (ALP), blood urea nitrogen (BUN), creatinine, total bilirubin, glucose, Na+, K+, Cl-, lactate dehydrogenase (LDH), creatine phosphokinase (CPK), and urine tests including dip-stick test and urine microscopy. Urinary human chorionic gonadotropin (hCG) level will be checked 14 days before the second visit for every participant with the possibility of pregnancy, experiencing lack of menstruation for less than 1 year since the last menstrual period.

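### The article does not say whether the Bonferroni correction covers both the P-value and the 95% interval for each dose; Dunnett's method would put both on one basis and recover a little power

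*Protocol article*

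**What the plan says.** All references are to the protocol article.

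- Study design and setting: "Selected participants will be assigned to 3 experimental groups and 1 placebo group". Three dose comparisons therefore share one control group.
- Statistical analysis, in the paragraph on general ANOVA and chi-squared or Fisher comparisons: "The size of the type I error caused due to multiple comparisons will be modified using Bonferroni's method". The number of comparisons in the family is not given.
- Statistical analysis, next paragraph, on the primary ANCOVA: "The estimates of mean differences between placebo and each SOCG group, the 95% confidence interval", together with a P-value. The recovery and remission analyses follow the same pattern: "Estimates of odds ratio of each SOCG group, 95% confidence interval", again with a P-value.
- Sample size: "The sample size of each group is 37", from a t-test "between the SOCG medium dose group and the placebo group" at a 5% level with 80% power and 5% dropout. The effect is not stated; "the sample size was calculated referring to a clinical trial of similar design involving patients with depression".

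The text does not say that the P-values are adjusted, that the intervals are unadjusted, or that the Bonferroni sentence covers the ANCOVA.

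**The concern.** A P-value and an interval for the same contrast should lead to the same conclusion. Naming a family-wise correction and then an unqualified 95% interval leaves room for a dose whose interval excludes zero while its corrected P-value exceeds 0.05. The trial is meant to identify a dose, so such a result would leave its main decision open to argument, and conclusions drawn from the intervals alone would not be protected at 5% across the three doses.

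There is also an efficiency point. Bonferroni makes no use of the known correlation of about 0.5 between contrasts that share a placebo group. Dunnett's method was built for this layout and gives the same family-wise protection with a slightly lower critical value.

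**Working it through.** **Inputs.** From the article: four equal groups, 37 per group, 5% level, 80% power, 5% dropout; the primary ANCOVA adjusts for group, baseline score and institution (two institutions). Assumed: two-sided testing, a family of three, 35 evaluable per group, and the effect size.

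**The plan's own figure.** 35/(1 − 0.05) = 36.8, rounded up to 37, and 4 × 37 = 148, so the arithmetic is consistent. The 35 itself cannot be recomputed because no difference or SD is given. Back-solving: (1.960 + 0.842) × √(2/35) = 0.670 with normal quantiles, or 0.679 with the noncentral t. I use 0.68 and also show 0.5.

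**Critical values.** Residual df = 140 − 4 − 1 − 1 = 134. The standard error of a difference is √(2/35) = 0.239 SD. Dunnett's value solves, for three equally correlated contrasts (0.5), P(max|T| ≤ c) = 0.95.

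| Basis | Critical value | Interval half-width (SD) | Family-wise error |
|---|---|---|---|
| Unadjusted | 1.978 | 0.473 | 12.5% |
| Bonferroni, three comparisons | 2.424 | 0.580 | 4.4% |
| Dunnett, single-step | 2.376 | 0.568 | 5.0% |

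Three ordinary 95% intervals have joint coverage of 100% − 12.5% = 87.5%. Bonferroni intervals are 2.424/2.376 = 1.02 times as wide as Dunnett's.

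**What each reading of the text gives.**
- P-values corrected (or alpha lowered to 0.05/3) and intervals ordinary: they disagree when 1.978 < |T| < 2.424, that is, raw p between 0.0167 and 0.05.
- Both corrected: they agree.
- The Bonferroni sentence does not reach the ANCOVA: they agree, but family-wise error is 12.5%.

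**Size of the disagreement under the first reading.** With noncentrality d/0.239:
- d = 0.68: P(|T| > 1.978) − P(|T| > 2.424) = 0.806 − 0.663 = 0.143, about 14%.
- d = 0.5: 0.5465 − 0.3727 = 0.174, about 17%.
- d = 0: 0.05 − 0.0167 = 0.033.

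By simulation at d = 0.68, at least one dose shows the disagreement in about 20% of trials if one dose works and about 35% if all three do.

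**Power per fully effective dose.** Bonferroni and single-step Dunnett from the noncentral t; step-down by simulation (1,000,000 runs per scenario), with thresholds 2.376, 2.236 and 1.978 applied to the ordered statistics.

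| Scenario | Bonferroni | Dunnett | Step-down Dunnett |
|---|---|---|---|
| d = 0.68, one dose works | 66.3% | 68.0% | 68.1% |
| d = 0.68, effects half/full/full | 66.3% | 68.0% | 71.5% |
| d = 0.68, all three work | 66.3% | 68.0% | 75.0% |
| d = 0.5, one dose works | 37.3% | 39.1% | 39.2% |
| d = 0.5, all three work | 37.3% | 39.1% | 44.9% |

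Every Dunnett threshold lies below 2.424, so both Dunnett versions reject whenever Bonferroni does.

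**Step-down tests beside single-step intervals.** At d = 0.68, a rejection sits beside an interval that includes zero in about 0.5% of comparisons if one dose works and about 7% if all three do. In the latter case this affects at least one dose in about 19% of trials.

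**The case against.** A reader might infer that the plan contradicts itself, with adjusted P-values beside unadjusted intervals. The article does not support that. It says neither. A Bonferroni simultaneous interval is also called a 95% interval, the Bonferroni sentence stands in the paragraph on general comparisons, and the full analysis plan, which is not shown, could settle the point. This objection stands: the mismatch is a possibility the wording allows, and on its own it is reporting detail.

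A reader might also conclude that Bonferroni is wrong or wastes much power. It is neither. It is prespecified, valid and holds family-wise error at 4.4%. Single-step Dunnett gains under 2 points, worth about one participant per group. The larger gain comes from stepping down rather than from using the correlation, and is large only if several doses work: Holm gives 66.3% with one effective dose and 74.0% with three. Stepping down also brings back some disagreement between test and interval.

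What remains is that Dunnett with its matching intervals fits this design, removes the ambiguity and is never less powerful than Bonferroni at the same 5% family-wise level.

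**Conclusion.** The point holds as an improvement to the choice and reporting of method, not as an error or a stated contradiction. The article should put test and interval on one declared basis. If it does not, and the P-values alone are corrected, about 14% to 17% of comparisons with a real effect would show conflicting evidence.

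The gain from single-step Dunnett is small but free: about 66% to 68% per effective dose at d = 0.68. Step-down testing gains about 2 points over Bonferroni if one dose works and about 9 if all three do, with the interval caveat above.

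These figures rest on two-sided testing, three comparisons, 35 evaluable per group and assumed effects of 0.5 to 0.68. The 12.5%, 4.4% and critical values do not depend on the effect size. The change does not restore 80% power per dose: the sample size was set for a single comparison at 5%.

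**What to change.** In Statistical analysis, for the three placebo comparisons in the primary ANCOVA:

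1. Replace Bonferroni by Dunnett's method, using the correlation from the fitted model, and report Dunnett-adjusted P-values with the matching simultaneous 95% intervals. Test and interval then always agree.
2. Alternatively, use step-down Dunnett for the test. State in advance that the single-step intervals are more conservative, so that a significant dose may have an interval that includes zero.
3. If Bonferroni is kept, name the family of three and report 98.33% intervals (1 − 0.05/3 = 0.9833).

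Label any unadjusted interval as descriptive, including those for the odds ratios if they are left uncorrected.

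The cost is a few sentences, settled before unblinding. It needs standard software and no extra participants, and family-wise error stays at 5%.

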## Abstract

**Introduction::**

Major depressive disorder (MDD) is a common condition worldwide, and leads to degradation in quality of life and large socioeconomic costs. There has been increasing demand for new therapies with fewer side effects. SOCG (SOCG tablet) is a modified prescription of So-ochim-tang, which is widely used in Traditional Korean Medicine to treat MDD. We aim to evaluate the efficacy of SOCG in treating MDD, and identify the optimum dose.

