SSRIs and tricyclic antidepressants (TCAs) have been reported to have significant antidepressant effects along with various side effects. The most common side effects of SSRIs are nausea, vomiting, diarrhea, stomach ache, hot flashes in the chest, and headache. 10% to 20% of patients experience insomnia, anxiety, and excitement, and 30% to 40% experience sexual dysfunction such as retarded ejection, erectile dysfunction, and decreased sexual desire. TCAs usually cause depersonalization, confusion, orthostatic hypotension, and sedation as initial symptoms and cloudy vision, severe thirst, weight gain, epilepsy, and extrapyramidal symptoms as later symptoms.^[8]^ In addition, Koreans are known to be 4 times poorer metabolizers via the hepatic enzymes compared to western populations, increasing the likelihood of toxicities.^[11]^ Therefore, new antidepressants suitable for use by Koreans are needed. In this regard, natural products have recently been receiving attention which have been due to their proven safety and effectiveness based on clinical experience. Herbal decoctions described in various Korean classical medical texts have shown effectiveness in treating MDD in clinical settings.

SOCG is a prescription containing So-ochim-tang combined with *Platycodonis Radix* and *Aurantii Fructus Immaturus*. So-ochim-tang is widely used for treatment of MDD and somatization disorder, which are thought to be caused due to stagnation of qi. Its use is mentioned in “Donguibogam”^[12]^ (“So-ochim-tang for … every qi-related problem”) to treat qi-related pains in the chest and abdomen. SOCG has been shown to have reasonable antidepressant activity in animal behavior studies compared to different antidepressant treatments. It has also been patented as a composition for treating depressive disorder^[13,14]^ (Registered patent of Republic of Korea 10-1910013). However, clinical effects in humans through well-designed trials have not been assessed.

In the present study, we aim to assess the efficacy and safety of orally administered SOCG in MDD patients and determine the appropriate dosage.

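### The trial aims to identify the optimum dose, but the stated primary analysis compares each dose only with placebo and does not directly address that aim

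*Protocol article*

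**What the plan says.** **Aim.** The abstract says "We aim to evaluate the efficacy of SOCG in treating MDD, and identify the optimum dose". The Introduction (section 1) repeats it: to "assess the efficacy and safety of orally administered SOCG in MDD patients and determine the appropriate dosage". The Discussion gives determining dosage as one reason for recruiting moderate to severe patients, and it makes confirmation of the appropriate dose part of the case for phase III.

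**Design.** Section 2.1: "The experimental groups will be a low dose group, a medium dose group, and a high dose group", plus a placebo group. Under section 2.4 the four arms take 0, 1, 2 or 3 active tablets out of three, so the doses are ordered and equally spaced.

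**Analysis.** Section 2.7.2 analyses the primary outcome by "analysis of covariance (ANCOVA) with the experimental group, baseline K-HDRS, and the institution as the explanatory variables". It then lists what will be presented: "The estimates of mean differences between placebo and each SOCG group, the 95% confidence interval" and the P-value. The linear mixed model in the same section is a sensitivity analysis for missing values. The logistic models for recovery and remission also take placebo as the reference. On multiplicity the section says only that "The size of the type I error caused due to multiple comparisons will be modified using" Bonferroni's method, without saying which comparisons are counted.

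**Sample size.** Section 2.7.1 sizes the trial on the comparison "between the SOCG medium dose group and the placebo group", "considering a significance level of 5%, a power of 80%, and assigning a ratio of 1:1:1:1 and a dropout rate of 5" percent.

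**The concern.** A dose-placebo difference answers whether that dose works. The optimum-dose aim asks how the doses compare with one another, or what the dose-response curve looks like. With group as an unordered factor, the three placebo differences share a control arm but borrow nothing from neighbouring doses, and no stated estimate sets one dose against another.

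What is at stake is the reading of the result. Suppose one or two doses reach significance and the rest do not. Nothing in the stated analysis would stop that pattern being taken as evidence of a best dose, although at about 35 patients per arm it arises readily when all doses are equally good. The article links confirmation of the appropriate dose to phase III, so a misreading would carry forward.

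**Working it through.** **1. The plan's own figure.** Section 2.7.1 gives 37 per group. With 5% dropout, 35 / 0.95 = 36.8, which rounds up to 37, and 4 × 37 = 148. The dropout step therefore reproduces from 35 evaluable per arm. The rest cannot be reproduced, because the article states no mean difference or SD.

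**2. Assumed effect size.** Back-solve n = 2((z_α + z_β)/d)² at n = 35 and 80% power:
- Two-sided 5%: d = (1.960 + 0.842) × √(2/35) = 0.670; with the t distribution, 0.68. This is the base case.
- One-sided 5% (sidedness is not stated): d = (1.645 + 0.842) × √(2/35) = 0.59. Lower end.
- Two-sided 0.05/3, t-based: d = 0.79. Upper end.

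**3. Precision between doses.** The half-width of the 95% interval is t(0.975, 68) × √(2/35) = 1.995 × 0.239 = 0.477 SD. Pooling the variance over four arms (136 df) gives 0.473. Either is about 70% of the assumed effect (0.477 / 0.68 = 0.70). To separate two doses that differ by half of 0.67 SD with 80% power takes 2 × (2.802 / 0.335)² ≈ 140 evaluable per arm.

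**4. How often the placebo tests disagree when all doses are equal.** Simulation of 400,000 trials per scenario: 35 per arm, unit SD, pooled variance on 136 df, Bonferroni over three tests (0.05/6 per side, critical t = 2.42). *Disagree* means that one or two of the three doses are significant.

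| Assumed d, same for all doses | Tests disagree, Bonferroni | Tests disagree, unadjusted 5% |
|---|---|---|
| 0.59 | 49% | 43% |
| 0.68 | 45% | 33% |
| 0.79 | 32% | 19% |

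With equal doses each one ranks best in a third of trials, whatever d is.

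**5. When the doses do differ.** If the curve is linear and reaches 0.67 SD at the high dose, the high dose ranks best in 81% of trials. If it reaches 0.67 SD at the medium dose and keeps rising, the figure is 92%. If it levels off at the medium dose, medium and high each rank best in about 49%.

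**6. A multiple-contrast test on the same data.** Optimal contrasts for linear, plateau and umbrella shapes over 0, 1, 2, 3 tablets; the largest of the three is tested at one-sided 2.5% (critical value 2.30). Power to detect activity at d = 0.68:

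| True shape (placebo, low, medium, high, as multiples of d) | Contrast test | At least one Bonferroni test significant |
|---|---|---|
| Flat: 0, 1, 1, 1 | 0.90 | 0.87 |
| Linear: 0, 1/3, 2/3, 1 | 0.79 | 0.70 |
| Low dose inactive: 0, 0, 1, 1 | 0.93 | 0.81 |
| Umbrella: 0, 1/2, 1, 1/2 | 0.75 | 0.69 |

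The contrast test was also higher for each of these shapes at d = 0.59 and d = 0.79. A single linear trend test would not do: at d = 0.67 its power is 42% against 67% under the umbrella, and 75% against 86% under the flat shape.

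**The case against.** The strongest objection is that this is a journal article. A dose-selection rule or dose-response model may sit in an analysis plan that is not shown, and pairwise comparison with placebo under multiplicity control is a valid phase II analysis. Both statements are true. The point therefore rests on what the article does fix: it names the estimates for the primary outcome, and these do not address a stated aim.

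Three stronger readings are tempting, and the documents do not support them.

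- *The planned analysis cannot identify the dose.* The ANCOVA yields adjusted means for all four arms, from which differences between doses could be taken, and under a linear curve the top-ranked dose is right in about 81% to 92% of trials. The general Bonferroni sentence could also be read as covering all pairwise comparisons, although the primary-outcome text names placebo differences only.
- *The dose will be picked by whichever P-value is significant.* No such rule is stated. Section 2.7.2 also reports estimates with confidence intervals and compares adverse events between groups, and the Discussion speaks of safety, efficacy and dose together. The 45% measures how weak the pattern of significance is as evidence; it is not the error rate of a stated rule.
- *The power gains show that the dose would be better chosen.* They concern detecting any activity.

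A further objection partly stands: the contrast test is not a dose-selection rule either. If the largest significant contrast were taken as the true shape at d = 0.68, the linear or umbrella shape would be selected in about 21% of trials with all doses equal, and the linear shape in about 75% of trials with an inactive low dose. The basic limit is information at 35 per arm, and no analysis removes it.

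**Conclusion.** The concern holds as a mismatch between a stated aim and the stated primary analysis. The placebo comparisons remain valid for what they test, but they do not directly address the dose question, and their pattern of significance is weak evidence about which dose is best: about 45% disagreement when the doses are equal (49% to 32% for d from 0.59 to 0.79), with about ±0.48 SD on any difference between two doses.

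These figures rest on a back-solved d that the article does not state, 35 evaluable per arm, Bonferroni over three tests (the article gives no count), and no gain from baseline adjustment. Adjustment that reduced the residual SD would narrow the intervals. The one-third ranking of equal doses does not depend on d.

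**What to change.** Keep the ANCOVA and the three dose-placebo differences. In the protocol and the analysis plan, before unblinding, add on the same model:

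- a multiple-contrast dose-response test over 0, 1, 2, 3 active tablets, with named candidate shapes (for example linear, plateau or Emax, and umbrella) and its type I error level;
- the fitted dose-response curve with its confidence band;
- differences between doses with 95% confidence intervals;
- a sentence saying that the dose conclusion rests on these estimates and their uncertainty together with tolerability, and neither on which placebo comparison reaches significance nor on which contrast is largest.

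If the analysis plan already contains such an analysis, the protocol text should say so.

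The cost is wording and a modest extra analysis, with no further patients or data. At the assumed d of 0.68 the contrast test also adds about 3 to 12 points of power to detect activity over requiring at least one significant Bonferroni test. The downside is that the candidate shapes must be fixed in advance. At 35 per arm, doses with similar effects will still not be separated, and the report should say so.
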